## Abstract

**Introduction:**

Heart failure with preserved ejection fraction (HFpEF) is a widespread public health issue worldwide. Despite recent advances in pharmacologic treatments and the introduction of new diagnostic approaches, HFpEF remains underdiagnosed and under-recognized in clinical practice. Traditional Chinese medicine (TCM) may offer a potentially effective treatment for HFpEF. Nevertheless, few clinical trials employ rigorous research methodologies to evaluate the efficacy and safety of TCM in treating HFpEF. Consequently, we propose to assess the hypothesis that patients with HFpEF may benefit from Fuzheng Yangxin Granule (FZYX) and evaluate its safety in a rigorously designed clinical trial.

**Methods:**

This multicenter, double-blind, randomized controlled trial will be conducted across seven tertiary hospitals in China. We will enroll 150 participants aged 18–80 years with confirmed HFpEF (Qi-Yin deficiency and blood stasis syndrome) meeting inclusion criteria. Participants will be randomly assigned (1:1) to the FZYX group or the placebo group, ​with both groups receiving standardized Western medical therapy according to the National Heart Failure Guideline 2023. The 12-week intervention phase will be followed by 40-week safety follow-up. The primary outcome will be maximal peak oxygen uptake (peak VO_2_). Secondary outcomes will include composite endpoint events, all-cause mortality, 6-minute walking distance (6MWD), New York Heart Association (NYHA) functional class, serum N-terminal pro-B-type natriuretic peptide (NT-proBNP), echocardiographic variables, Minnesota Living with Heart Failure Questionnaire (MLHFQ) score, TCM syndrome scores, and the FRAIL scale.

**Discussion:**

The objective of this study is to evaluate the efficacy and safety of FZYX in treating HFpEF (Qi-Yin deficiency and blood stasis syndrome), thereby providing a high-quality, reliable evidence-based foundation for clinical practice.

**Clinical Trial Registration:**

China Clinical Trial Registry (ChiCTR2400087293), Registered on July 24, 2024.

## Introduction

1

Heart failure with preserved ejection fraction (HFpEF) is not merely a single pathological diagnosis but a complex clinical syndrome characterized by a left ventricular ejection fraction (LVEF) ≥ 50%, along with symptoms such as dyspnea and weakness (1). HFpEF is estimated to account for approximately 50% of all heart failure cases (2), with a 5-year survival rate of 35%–40% following the first hospitalization (3). And a 5-year mortality rate comparable to that of heart failure with reduced ejection fraction (HFrEF) (4).

Due to the heterogeneous pathophysiological mechanisms of HFpEF, evidence-based treatment and diagnosis rely primarily on clinical symptoms, signs, and evidence of structural and/or functional cardiac abnormalities. Despite significant efforts by scholars to develop treatments for HFpEF, translating preclinical experimental medicine into clinical practice remains a challenge. For example, trials targeting the renin-angiotensin system (RAS) [PEP-CHF trial (5), I-PRESERVE study (6), CHARM-Preserved study (7)], mineralocorticoid receptor antagonists (MRA) [TOPCAT study (8)], beta-blockers [OPTIMIZE-HF study (9)], and digitalis [DIG-PEF study (10)] have been conducted. None of these trials have demonstrated that conventional heart failure treatments effectively reduce mortality, readmission rates, or improve prognosis in HFpEF. These include trials investigating nitrate drugs [NEAT-HFPEF study (11)], inhaled nitrites [INDIE-HFpEF study (12)], soluble guanylate cyclase agonists [DILATE-1 study (13)], phosphodiesterase-5 inhibitors [RELAX study (14)], SGLT2 inhibitors [CANVAS study (15), DECLARE-TIMI 58 trial (16), EMPEROR-Preserved study (17)], and angiotensin receptor neprilysin inhibitors (ARNI) [PARAGON-HF trial (18)].

Most of these trials did not yield satisfactory results; however, the EMPEROR-Preserved study (17) is the first successful clinical trial for HFpEF. The study found that Empagliflozin significantly reduced the incidence of the composite endpoint of cardiovascular death or heart failure hospitalization (HHF) compared to placebo. The PARAGON-HF trial (18) did not show a statistically significant difference in primary endpoint events (cardiovascular death and heart failure hospitalization) compared to valsartan (*P* = 0.0585). Additionally, a trend of benefit was observed in two subgroups: women (HR = 0.73, 95% CI: 0.59–0.90) and LVEF ≤ 57% (HR = 0.78, 95% CI: 0.64–0.95). The 2023 Focused Update of the 2021 ESC Heart Failure Guidelines classified SGLT2 inhibitors as a class 1A recommendation (19). Enhancing the precision of treatment strategies through the development of specific drugs for HFpEF remains a crucial area of ongoing research.

HFpEF is a significant public health concern, and relying solely on modern medical treatments is insufficient for effective management. As the understanding of HFpEF in traditional Chinese medicine (TCM) grows, numerous scholars have conducted extensive studies on TCM treatment protocols and clinical efficacy evaluations for HFpEF. Their findings indicate that TCM offers distinctive advantages in improving clinical symptoms, cardiac function, and quality of life in HFpEF patients (20). A 2018 meta-analysis of 17 randomized controlled trials (RCTs) reported that TCM combined with western medicine effectively improved exercise tolerance and quality of life in HFpEF patients (21). The Chinese medicine QishenYiqi pill has been shown to improve cardiac function and inhibit myocardial fibrosis in HFpEF mice by reducing microvascular endothelial inflammation and activating the NO-cGMP-PKG pathway (22). Therefore, TCM's advantages can be fully utilized to intervene at various stages of HFpEF onset and progression, addressing multiple targets and pathways.

Although numerous clinical trials have been conducted to assess the efficacy and safety of TCM since the first RCT was published in 1982 (23), most current studies are small-scale, low-quality trials, case reports, or clinical experience reports. Additionally, the reliability of study results, report completeness, and their relevance for guiding clinical practice have been questioned (24). The evidence supporting TCM diagnosis and treatment remains widely unaccepted, limiting its broader promotion and application.

According to the Guidelines for Diagnosis and Treatment of Chronic Heart Failure in Traditional Chinese Medicine (2022) (25), the TCM syndrome types for HFpEF include Qi deficiency with blood stasis, Qi-Yin deficiency with blood stasis, and Yang-Qi deficiency with blood stasis. Through long-term treatment and observation of HFpEF patients, we found that they exhibit deficiencies in Qi, blood, Yin, and Yang, along with blood stasis, characterized by symptoms like palpitations, shortness of breath, weakness, exertional sweating, spontaneous or nocturnal sweating, cyanosis of the lips and tongue, and a thin, astringent, intermittent, or weak pulse. Therefore, Qi-Yin deficiency with blood stasis is the most common pattern, prompting us to develop the Fuzheng Yangxin Granule (FZYX). We plan to conduct a rigorously designed RCT to evaluate the efficacy and safety of FZYX in treating HFpEF with Qi-Yin deficiency and blood stasis syndrome.

## Methods and analysis

2

### Study design

2.1

This study is designed as a randomized, double-blind, placebo-controlled, parallel-group, multicenter trial. The study design follows the Standard Protocol Items: Recommendations for Interventional Trials (SPIRIT) Guidelines (26). Seven tertiary hospitals across different regions of China are participating in this trial. A total of 150 stable HFpEF patients meeting the inclusion and exclusion criteria will be randomized 1:1 into either the experimental or control group. The overall design of the trial is presented in Figure 1.

**Figure 1 F1:**
[figure not shown]
Flow chart of the trial. HFpEF, heart failure with preserved ejection fraction; FZYX, Fuzheng Yangxin Granule.

### Sample size estimation

2.2

The primary efficacy index of this trial is peak oxygen uptake (peak VO2), as demonstrated in previous related studies (27–29). It is anticipated that the peak oxygen uptake after treatment will be 16 ml/kg/min in the control group and 17.6 ml/kg/min in the experimental group, with a standard deviation of 3.1 ml/kg/min between the two groups. The sample size was calculated using PASS 15.0. The sample size was estimated by comparing the means of two samples in a completely randomized design, using a two-sided test with a significance level of *α* = 0.05 and power (1-*β*) of 0.80. With a 1:1 allocation between the experimental and control groups, the sample size for each group was estimated to be 60 participants. Considering a potential 20% attrition rate, 75 participants were included in each group, resulting in a total of 150 participants.

### Inclusion criteria

2.3

Participants aged 18–80 years, irrespective of gender.Participants diagnosed with Qi-Yin deficiency and blood stasis syndrome, as defined by Traditional Chinese Medicine (TCM) principles: Patients must present with at least two of three cardinal symptoms (shortness of breath/dyspnea, fatigue, or palpitations) combined with two of four secondary symptoms (persistent thirst/dry pharynx, spontaneous daytime sweating exacerbated by activity or night sweating ceasing upon awakening, heat sensation in palms/soles, or cyanotic facial/lip discoloration). Characteristic tongue manifestations include dark red or purplish coloration with ecchymosis/petechiae/varicose sublingual veins, thin body with scanty, absent, peeled, or fissured coating. Pulse findings must demonstrate thready-rapid-weak characteristics or irregular-intermittent rhythm. Syndrome confirmation requires concurrent fulfillment of symptom criteria and corresponding tongue-pulse presentations.New York Heart Association (NYHA) functional class II-III with hemodynamic stability.Meeting the diagnostic criteria for HFpEF as outlined in the National Heart Failure Guideline 2023 (30).
(a)Epidemiological and population characteristics of HFpEF patients;(b)Signs and/or symptoms of heart failure;(c)LVEF ≥ 50%;(d)Objective evidence of cardiac structural and/or functional abnormalities consistent with left ventricular diastolic dysfunction and/or elevated left ventricular filling pressures. This includes: (i) E/e’ >15, (ii) Septal e’ <7 cm/s or Lateral e’ <10 cm/s, (iii) tricuspid regurgitant velocity >2.8 m/s or estimated PASP > 35 mmHg, (iv) elevated LAVI (sinus rhythm: LAVI >34 ml/m^2^, atrial fibrillation: LAVI > 40 ml/m^2^), and (v) elevated natriuretic peptide levels.Voluntary participation, with participants providing informed consent after understanding the study details.

### Exclusion criteria

2.4

Any prior echocardiographic LVEF measurement <40%.Uncontrolled hypertension, defined as resting systolic blood pressure ≥180 mmHg and/or diastolic blood pressure ≥110 mmHg, confirmed at two separate examinations before randomization.ALT, AST, or bilirubin levels exceeding 3 times the upper limit of normal (not due to heart failure), glomerular filtration rate <15 ml/min/1.73 m^2^, and blood potassium >5.5 mmol/L.Within 3 months of: acute coronary syndrome, stroke, transient ischemic attack, cardiac, carotid, or other major vascular surgery, PCI, carotid angioplasty, coronary artery bypass grafting, or any non-cardiac condition that may impair exercise capacity or be exacerbated by strenuous exercise (e.g., infection, liver/kidney failure, thyrotoxicosis).Patients with severe primary diseases affecting the liver, kidneys, hematopoietic, nervous, or endocrine systems, tumors, or psychiatric disorders.Life expectancy of less than one year.Known allergies to any trial medications.Participation in other drug trials within the last month.Patients currently using Chinese medicine or patent medicines containing ingredients similar to FZYX.Pregnancy (confirmed by a positive test if needed), lactation, or women of childbearing age not using effective contraception.Patients deemed unable to complete or comply with the study requirements, per investigator's judgement.

### Randomization and blinding

2.5

A computer-generated blocked randomization scheme will be implemented using permuted blocks of 6 participants (3 FZYX:3 placebo) to ensure balanced allocation throughout recruitment. An independent statistician will generate the randomization sequence with consecutive numbering from 001 to 150 assigned to pre-packaged, identical medication bags. Participants will be sequentially enrolled and allocated medications strictly according to their entry order, with each bag containing either FZYX or placebo labeled only with the corresponding randomization code. The allocation list will remain securely encrypted in a password-protected file accessible solely to the independent statistician until database lock. This double-blind design ensures concealment from participants, investigators, outcome assessors, and data analysts throughout the trial duration.

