#### Primary outcome

2.8.1

The primary evaluation measure is peak VO_2_.

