### Statistical collection and analysis

2.10

Study data will be collected at each center using standardized paper-based Case Report Forms (CRFs). Participants will be provided with a private space to complete the quality of life form to address privacy concerns. Two-tailed tests will be applied with *P* < 0.05 as the significance threshold. No adjustments for multiple testing will be performed for secondary endpoints, as they are exploratory. Analyses will be conducted using SPSS 23.0 and R 4.3.1. Primary outcome: Analyzed using ANCOVA adjusted for baseline peak VO₂, age, and sex. Secondary continuous outcomes: Assessed via mixed-effects models for repeated measures. Non-normally distributed data will use bootstrap CIs (10,000 replications). Binary/categorical data: Analyzed using chi-squared or Fisher's exact test. Ordinal outcomes: Evaluated via proportional odds models.

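### Centre enters neither the allocation list, as described, nor the primary ANCOVA, so arms are balanced overall but not within hospitals; adding centre is cheap insurance for precision

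*Protocol article*

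**What the plan says.** Study design, section 2.1: "Seven tertiary hospitals across different regions of China are participating in this trial".

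Randomization and blinding, section 2.5, describes a blocked scheme "using permuted blocks of 6 participants (3 FZYX:3 placebo) to ensure balanced allocation throughout recruitment". The independent statistician is to "generate the randomization sequence with consecutive numbering from 001 to 150 assigned to pre-packaged, identical medication bags". The dispensing rule is "Participants will be sequentially enrolled and allocated medications strictly according to their entry order". No stratification factor is named, and no range of numbers is reserved for a hospital.

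Primary outcome, section 2.8.1: "The primary evaluation measure is peak VO_2". Table 2 schedules the exercise test at Visit 1 and Visit 4.

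Statistical collection and analysis, section 2.10, gives the primary model: "Analyzed using ANCOVA adjusted for baseline peak VO₂, age, and sex". Secondary continuous outcomes go to mixed-effects models for repeated measures. Centre is mentioned for neither.

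**The concern.** Blocking one list by entry order balances the arms over calendar time. It does nothing to balance them inside a hospital, because each block of 6 is scattered over whichever hospitals recruit next. With 150 patients in seven hospitals (about 21 each), sizeable within-hospital imbalances can arise by chance.

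If hospitals also differ in week-12 peak VO2 for reasons the covariates do not capture, two things follow. That variation sits in the error term and widens the confidence interval. In any one trial, it also shifts the estimate by chance when a high or low hospital happens to hold more of one arm. A centre term deals with both, and the primary model as stated has none. The covariate set is written out in the article, so this is a stated choice rather than a detail left to an analysis plan.

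**Working it through.** **1. The plan's own figure.** Inputs from section 2.2: means of "16 ml/kg/min in the control group and 17.6 ml/kg/min in the experimental group" (difference 1.6), SD 3.1, two-sided alpha 0.05, power 0.80.

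n per arm = 2 × (1.960 + 0.842)² × (3.1/1.6)² = 2 × 7.85 × 3.754 ≈ 58.9, so 59 by the normal approximation. The noncentral t gives power 0.794 at 59 and 0.8006 at 60, so 60 per arm. Then 60/0.80 = 75 per arm, 150 in total. The stated size reproduces and does not depend on the centre question.

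**2. Imbalance within hospital.** Let D be the arm difference in one hospital and let each patient fall in that hospital with probability 1/7 (assumed equal recruitment). The list sums to zero over arms, so

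Var(D) = 150 × (1/7) × (6/7) = 18.4, SD = 4.3 patients.

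Simulating 20,000 lists of 25 blocks of 6 gives SD 4.27 and a 58% chance that at least one hospital is split 2:1 or worse. Fixing hospital sizes at 21 or 22 gives 60%, with 9% for 3:1 or worse. An assumed uneven pattern of 60/30/20/15/10/8/7 gives 83% and 45%. Blocks of 6 run within hospital would cap the difference at 3.

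**3. Chance shift of the estimate.** With between-hospital SD s left after adjustment, the difference in means moves by the sum of (site effect × D)/75 over seven hospitals:

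SD of shift = s × √(7 × 18.4)/75 ≈ 0.15 s.

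For s = 1 ml/kg/min (assumed) that is 0.15, about 9% of the planned 1.6. Its average over allocations is zero.

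**4. What baseline peak VO2 already removes.** Assume that site explains a share ICC of the variance, that the baseline to week-12 correlation within site is 0.7, and that the SD is 3.1. The documents give no ICC or correlation.

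- *Site differences identical at both tests, ICC 0.10.* Slope = 0.10 + 0.90 × 0.7 = 0.73. Site part = 0.10 × (1 - 0.73)² = 0.0073. Within part = 0.90 × (1 + 0.73² - 2 × 0.73 × 0.7) = 0.460. Site share of residual variance = 0.0073/0.467 = 1.6% (2.7% at ICC 0.20).
- *Site effects at the two tests unrelated, ICC 0.10.* Slope = 0.63. Site part = 0.10 × (1 + 0.63²) = 0.140. Within part = 0.463. Share = 23% (38% at ICC 0.20).

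So only site variation that changes between Visits 1 and 4, or site differences in response, remains for a centre term to remove.

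**5. Power with and without centre.** N = 120 completers and an illustrative difference of 1.2. The within-site residual SD is 3.1 × √(0.90 × 0.51) = 2.10. Residual df without centre = 120 - 5 = 115; with centre = 109.

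- With centre: SE = 2.1 × √(4/120) = 0.383, inflated by about √(1/(1 - 6/119)) = 1.026 because arm and hospital are not orthogonal, giving 0.393. Power is about 0.85 to 0.86.
- Without centre: SE = √(2.1² + (6/7)s²) × √(4/120), where 6/7 allows for only seven hospitals.

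| Residual site SD s | SE without centre | Power without | Change from adding centre |
|---|---|---|---|
| 0 | 0.383 | 0.87 | about -2 points |
| 1.0 | 0.419 | 0.81 | about +5 points |
| 1.5 | 0.460 | 0.74 | about +12 points |

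Simulation agrees. In full ANCOVA simulations with baseline included, type I error stayed between 0.044 and 0.056 with or without centre.

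**The case against.** The strongest reply is that the planned model already handles most of this. Baseline peak VO2 is a covariate, and lasting differences between hospitals in calibration or case mix appear in it. If those differences are stable, a centre term gains nothing: at ICC 0.10 simulated power is 0.858 without centre and 0.849 with it. That stands, and it is why no definite power loss is claimed. A reader might infer that between-site variation in exercise testing simply stays in the error term; the baseline adjustment in section 2.10 rules that out.

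It can also be said that a 2:1 split in the worst of seven hospitals says little about a pooled contrast planned at 75 against 75. This is right as to validity. A reader might infer bias or a false-positive problem; neither the design nor the simulations support that.

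Third, a single list is an inference. The full protocol may give ranges of numbers to hospitals, with entry order read per hospital. The article does not exclude this, although consecutive numbering used by entry order points the other way.

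Two further readings are unsupported. The article does not say that each hospital tests on its own equipment with its own staff, or manages background therapy in its own way; sections 2.6 and 2.11 speak of standardised therapy and training. Nor does the published block size threaten concealment under the present scheme: with one double-blind list across seven hospitals, a site sees only scattered members of each block.

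What remains is that the stated model omits centre, and the possible gain from including it exceeds the certain cost.

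**Conclusion.** The point holds as a cheap improvement in precision. As described, allocation is not balanced within hospital, and with equal recruitment a 2:1 or worse split somewhere is more likely than not (58%). Uneven recruitment makes it likelier. The consequence is possible loss of precision and chance association of arm with hospital. The sample size of 150 stands and the test remains valid.

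The size of the gain is an assumption, because the article gives no between-site variance, no baseline to week-12 correlation and no hospital sizes. Over the range examined it runs from about -2 power points (no residual site variation) to about +12 (residual site SD 1.5 ml/kg/min), for an illustrative difference of 1.2 that is not the planned effect.

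**What to change.** Add centre to the primary ANCOVA and to the mixed models for secondary continuous outcomes, as a fixed or random effect. State a rule for pooling very small centres, and prespecify all of it before unblinding. This suffices if allocation has already begun.

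If allocation has not begun, also stratify the list by centre. Use varied, undisclosed block sizes, because a known fixed block of 6 is easier to exploit once whole blocks sit at one hospital. Supply further blocks on demand rather than fixed quotas, since near-equal recruitment is not documented. If ranges of numbers are already reserved for hospitals, section 2.5 should say so.

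Cost: 6 degrees of freedom out of about 115, at most about 2 power points under the present list (nearly all recovered by stratifying), and handling of unused medication bags per site. The sample size does not change.

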### Intervention

2.6

Following randomization, participants will receive either FZYX or matched placebo orally (2 sachets three times daily) for 12 weeks, with both preparations manufactured under Good Manufacturing Practice (GMP) standards at Xiyuan Hospital's pharmaceutical facility. The investigational products will be distributed through a serialized tracking system managed by the principal investigator, with documentation of batch numbers, dispensing dates, and return quantities. All participants will concurrently receive guideline-directed standardized medical therapy including: (1) sodium-glucose cotransporter-2 inhibitors (SGLT2i: empagliflozin/dapagliflozin) for HFpEF management; (2) diuretics for fluid-overloaded patients (NYHA II-IV); (3) angiotensin receptor-neprilysin inhibitors (ARNI: sacubitril/valsartan) indicated for symptomatic females [any left ventricular ejection fraction (LVEF)] or males (LVEF <55%–60%); (4) mineralocorticoid receptor antagonists (MRA: spironolactone) indicated for symptomatic females (any LVEF) or males (LVEF <55%–60%); (5) stable regimens for comorbidities (e.g., hypertension/diabetes). FZYX's herbal composition (see Table 1) and placebo share identical organoleptic properties through standardized production protocols.

**Table 1 T1:** Composition of FZYX.

Herbal name	Latin name	Dosage (g)
Ren Shen	Ginseng Radix Et Rhizoma	20
Huang Qi	Astragali Radix	30
Mai Dong	Ophiopogonis Radix	20
Di Huang	Rehmanniae Radix	15
Dang Gui	Angelicae Sinensis Radix	15
Hong Jing Tian	Rhodiolae Crenulatae Radix Et Rhizoma	30
Fu Zi	Aconiti Lateralis Radix Praeparata	10
San Qi	Notoginseng Radix Et Rhizoma	6

